### Diagnostic criteria

2.6

#### Diagnostic criteria of T2DM

2.6.1

According to the diagnostic criteria for T2DM in the *Standards of Medical Care in Diabetes-2020*^[6]^ issued by the American Diabetes Association in 2020: FPG ≥126 mg/dL (7.0 mmol/L). Fasting is defined as no caloric intake for at least 8 hours or 2-hour PG ≥200 mg/dL (11.1 mmol/L) during OGTT. The test should be performed as described by the WHO, using a glucose load containing the equivalent of 75 g anhydrous glucose dissolved in water or A_1_C ≥6.5% (48 mmol/mol). The test should be performed in a laboratory using a method that is NGSP certified and standardized to the DCCT assay or in a patient with classic symptoms of hyperglycemia or hyperglycemic crisis, a random plasma glucose ≥200 mg/dL (11.1 mmol/L).

### Diagnostic criteria of VCI

2.7

According to Guidelines from the Vascular Impairment of Cognition Classification Consensus Study, VCICCS, and Chinese Guide to the Diagnosis and Treatment of Vascular Cognitive Impairment (2019):^[1,2]^

#### Diagnostic criteria of cognitive impairment

2.7.1

Clinically significant deficits of sufficient severity in at least one cognitive domain (deficits maybe present in multiple domains) and severe disruption to instrumental activity of Daily living scale (IADLs)/ADLs (independent of the motor/sensory sequelae of the vascular event). A clear temporal relationship (within 6 months) between a vascular event and onset of cognitive deficits is only required for a diagnosis of post-stroke dementia.

### Diagnostic criteria of vascular etiology

2.8

#### Imaging criteria

2.8.1

Neuroimaging tests need to meet the minimum imaging criteria for the diagnosis of VCI by VASCOG, that is, at least one of the following imaging findings: one large vessel cerebral infarction is sufficient to cause VaMCI, whereas the diagnosis of severe VCI usually requires two or more large vessel cerebral infarct; the presence of an extensive or critical cerebral infarction in the thalamus or basal ganglia region may be sufficient to cause severe VCI; there were >2 luminal infarcts outside the brain stem (The luminal infarction of 1 to 2 key parts or 1 to 2 non-key parts combined with extensive white matter hyperintensity); extensive or fused white matter high signal; cerebral hemorrhage in key areas, or ≥2 cerebral hemorrhage; . a combination of the above forms.

#### Clinical manifestation standard

2.8.2

Clinical features need to meet one of the following criteria: there is a time correlation between the occurrence of cognitive impairment and ≥1 cerebrovascular events (the occurrence of cognitive impairment should be within 6 months after the cerebrovascular event, and the cognitive impairment is irreversible, and the cognitive impairment is often sudden. With the occurrence of many similar cerebrovascular events, it shows step-by-step progress or volatility, lasting more than 3 months); in the absence of cerebral vascular events, patients should have evidence of significant impairment of information processing speed, complex attention, significant impairment of frontal executive function. The following features can be used as support points: early gait abnormalities, including walking imbalance or repeated falls; early occurrence of frequent urination, urgent urination, or other symptoms that cannot be explained by urinary diseases; personality or emotional changes, such as loss of willpower, depression, or emotional incontinence.

### Inclusion criteria

2.9

#### Inclusion criteria of VCI patients with T2DM

2.9.1

1.It conforms to the diagnostic points of T2DM and VCI, and has been confirmed to have suffered from ischemic or hemorrhagic stroke by CT or MRI.2.With cognitive impairment, the score of the Montreal Cognitive Assessment scale (MoCA-Beijing version) is <26 (if the length of education is <12 years, one point is added to the test results to correct the cultural influence). The overall cognitive function is fully preserved, and the score of Mini Mental State scale (MMSE) ≥24. It did not meet the diagnostic criteria of dementia in the fourth edition of the American Diagnostic and Statistical Manual of Mental Disorders, with a clinical dementia scale (CDR) score of 0.5. Activities of daily living (ADL) were not significantly impaired, and the IADL score ≥16.3.Can cooperate to complete fMRI scan.4.The course of stroke ranges from 3 to 12 months.5.The range of age from 50 to 60 years old, right-handedness.6.No verbal language dysfunction.7.Have not received acupuncture or rehabilitation treatment in the past three months.8.Not accompanied by depression, mental symptoms and infectious diseases.9.The following categories of drugs were not used within 30 days before screening for cognitive impairment: drugs for the treatment of Alzheimer disease or dementia, anti-Parkinson disease drugs, short-acting antianxiety agents, nerve sedatives or analgesics, antiepileptic drugs, hormones, drugs with significant cholinergic or anticholinergic side effects.

### Inclusion criteria for patients with normal cognitive function in T2DM

2.10

1.Meet the diagnostic criteria of T2DM, and was confirmed by CT or MRI to exclude stroke.2.Cognitive function is normal, MoCA score ≥26 points (if the length of education is <12 years, one point is added to the test results to correct the cultural influence). MMSE score ≥24.CDR score is 0.IADL score ≥16.3.Can cooperate to complete fMRI scan.4.The range of age from 50 to 60 years’ old, right-handedness.5.No verbal language dysfunction.6.Have not received acupuncture or rehabilitation treatment in the past 3 months.7.Not accompanied by depression, mental symptoms, and infectious diseases.8.The following categories of drugs were not used within 30 days before screening for cognitive impairment: drugs for the treatment of Alzheimer disease or dementia, anti-Parkinson disease drugs, short-acting antianxiety agents, nerve sedatives or analgesics, antiepileptic drugs, hormones, drugs with significant cholinergic or anticholinergic side effects.

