**Methods/Design::**

A partial randomized controlled trial will be conducted at the Second Affiliated Hospital of Heilongjiang University of Chinese Medicine, between July 1, 2021 and December 31, 2023. A total of 80 subjects will participate in the trial, including 25 healthy volunteers, 25 T2DM patients with normal cognitive function and 30 VCI patients with T2DM. They will all have at least 1 functional magnetic resonance imaging scan. Through the calculation and analysis of voxel-based morphological analysis indexes, the changes of hippocampal volume and function in the 3 groups are compared, so as to confirm the correlation between hippocampal structural and functional changes, between T2DM patients and healthy volunteers, as well as T2DM patients with normal cognitive and VCI patients with T2DM. Then the VCI patients with T2DM were randomly divided into 2 groups. The control group was given routine drug treatment to control blood sugar and improve cognitive function, and the experimental group was treated with acupuncture-rehabilitation therapy on the basis of the control group. Patients in both groups will receive serum biomarkers (superoxide organic dismutase, maleic dialdehyde, brain-derived neurotrophic factor) detection and neuropsychological scale (Montreal Cognitive Assessment, Webster Memory Scale IV Chinese version (adult version), functional independent measurement) evaluation before treatment, 4 weeks, 8 weeks, and 12 weeks after treatment. The functional magnetic resonance imaging scan will be performed again after 12 weeks of treatment. To observe the effect of acupuncture-rehabilitation therapy on cognitive function of VCI patients with T2DM.

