### Trial design

2.2

This is an outcome assessor- and data analyst-blinded, partial randomized controlled trial conducted at the Second Affiliated Hospital of Heilongjiang University of Chinese Medicine from January 1, 2021 to December 31, 2023. A total of 80 subjects who met the inclusion criteria including 25 healthy volunteers, 25 T2DM patients with normal cognitive function, and 30 patients with VCI combined with T2DM were recruited into the study. First, they were scanned by fMRI, through the calculation and analysis of VBM indexes, the changes in hippocampal volume and function in the 3 groups of patients were compared to determine the difference between type 2 diabetes patients and healthy volunteers, correlation between hippocampal structural and functional changes in patients with normal cognitive T2DM and VCI patients with T2DM. Then, 30 VCI patients with T2DM were randomly divided into the experimental group and the control group, the control group was given routine drug therapy to control blood glucose and improve cognitive function, the experimental group was given acupuncture-rehabilitation therapy on the basis of the control group. The primary outcomes were obtained by VBM calculation and serum biomarkers (SOD, MDA, BDNF) detection, and the secondary outcome indexes were assessed by neuropsychological scales such as Montreal Cognitive Assessment (MoCA), Wechsler Memory Scale IV edition (WMS-IV), FIM, among others. Serum biological indicators and neuropsychological scale will be conducted before treatment, as well as 4 weeks, 8 weeks, and 12 weeks after treatment respectively, fMRI scan will be conducted before treatment and 12 weeks after treatment respectively, to observe the intervention effect of acupuncture-rehabilitation therapy on cognitive function of VCI patients with T2DM. Figure 1 and Table 1*present the technology roadmap and clinical observation flow charts, respectively.*

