### Inclusion criteria of healthy volunteers

2.11

1.Do not meet the diagnostic criteria for diabetes, and stroke is excluded as confirmed by CT or MRI.2.Cognitive function is normal, MoCA score ≥26 points (if the length of education is <12 years, 1 point is added to the test results to correct the cultural influence). MMSE score ≥24.CDR score is 0.IADL score ≥16.3.Can cooperate to complete fMRI scan.4.The range of age from 50 to 60 years’ old, right-handedness.5.Diseases without brain trauma, drug and alcohol dependence that may affect the structure and function of the brain, not accompanied by depression, mental symptoms and other diseases.

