#### Statistical processing and result presentation of brain function data

2.29.2

Statistical analysis is carried out by using DPASFA, SPM12, Xjview, Rest, and other software based on MATLAB platform.

The values of VBM, ReHo, and FC of healthy volunteers, T2DM cognitive normal group, and VCI group with T2DM were analyzed by ANOVA, with sex, age and years of education as covariates. The test level was set to: cluster level *P* < .05 (FWE or FDR correction). If *P* < .05 and could at least pass the FDR correction, there was a significant difference between the 2 groups of patients and healthy volunteers, which was statistically significant.

In the VCI group with T2DM, the data of VBM, ReHo, and FC in the experimental group and the control group were compared by double-sample *t* test. Paired-sample *t* test was used for intra-group comparison between the 2 groups before and after treatment. The test level was set as: cluster level *P* < .05 (FWE or FDR correction). If *P* < .05 and could at least pass the FDR correction, it was considered that there was a significant difference between the experimental group and the control group, which was statistically significant.

The statistical results were presented by Xjview and Mricron software.

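### In the three-group imaging comparison, stroke and cognitive impairment are completely aliased by the entry criteria, so hippocampal differences involving the VCI group cannot be assigned to one rather than the other

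*Protocol article*

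**What the plan says.** Section 2.2 (Trial design) enrols three groups: "including 25 healthy volunteers, 25 T2DM patients with normal cognitive function, and 30 patients with VCI combined with T2DM". All are scanned at baseline. The Abstract (Methods/Design) gives the purpose of this stage: "the changes of hippocampal volume and function in the 3 groups are compared, so as to confirm the correlation between hippocampal structural and functional changes". The contrasts it names are T2DM patients against healthy volunteers, and T2DM with normal cognition against VCI with T2DM.

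The entry criteria fix stroke status in each group:

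- VCI with T2DM (section 2.9.1): each patient "has been confirmed to have suffered from ischemic or hemorrhagic stroke by CT or MRI", and "The course of stroke ranges from 3 to 12 months".
- T2DM with normal cognition (section 2.10): "Meet the diagnostic criteria of T2DM, and was confirmed by CT or MRI to exclude stroke".
- Healthy volunteers (section 2.11): "Do not meet the diagnostic criteria for diabetes, and stroke is excluded as confirmed by CT or MRI".

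Cognitive status is fixed in the same way. MoCA must be below 26 in the VCI group and at least 26 in the other two.

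Section 2.29.2 states that the VBM, ReHo and FC values of the three groups are "analyzed by ANOVA, with sex, age and years of education as covariates".

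**The concern.** The natural use of the contrast between T2DM with normal cognition and VCI with T2DM is to read a smaller or less active hippocampus as the imaging counterpart of cognitive impairment in diabetes. Under these criteria the two groups also differ, without exception, in having had an ischemic or hemorrhagic stroke in the past year. The same holds for VCI against healthy volunteers, where diabetes differs as well.

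If the stroke itself changes hippocampal volume or function, the analysis will show a group difference even when cognitive impairment as such makes no contribution. Because the confounding comes from eligibility, a later statistical analysis plan cannot remove it from this contrast.

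**Working it through.** No figure in the article bears on this point, so there is none to reproduce. The check is whether the planned groups allow the two effects to be told apart.

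**Inputs.** Group sizes 25 / 25 / 30 (section 2.2); stroke and cognitive status by group (sections 2.9.1, 2.10, 2.11); covariates sex, age and years of education (section 2.29.2).

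| Group | n | T2DM | Cognitive impairment | Stroke |
|---|---|---|---|---|
| Healthy volunteers | 25 | 0 | 0 | 0 |
| T2DM, normal cognition | 25 | 1 | 0 | 0 |
| VCI with T2DM | 30 | 1 | 1 | 1 |

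The last two columns are identical: 30/30 in the VCI group and 0/(25 + 25) = 0/50 in the comparators.

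**Step 1: the planned model.** Write a hippocampal measure as

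y = b0 + b1·T2DM + b2·impairment + b3·stroke + covariates + error.

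Since impairment = stroke for every participant, the model reduces to

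y = b0 + b1·T2DM + (b2 + b3)·VCI group + covariates + error.

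Only the sum b2 + b3 can be estimated. In a numerical check with 80 participants and simulated values for the three covariates, the design matrix had 7 columns and rank 6. The two indicators correlated at 1.00. More participants in the same three groups would not change the rank.

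**Step 2: which contrasts are affected.**

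- VCI with T2DM against T2DM-normal estimates b2 + b3: affected.
- VCI with T2DM against healthy estimates b1 + b2 + b3: affected.
- T2DM-normal against healthy estimates b1: not affected, as both groups are stroke-free.
- Experimental against control within the VCI group: not biased by this, as every patient in both arms has had a stroke and allocation is random.

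**Step 3: would a lesion covariate rescue the three-group contrast?** Lesion volume could replace the stroke indicator and the matrix would then have full rank. But lesion volume is zero in all 50 comparators, so the adjusted difference would be an extrapolation to VCI patients with no lesion, of whom there are none. Full separation needs a group that breaks the tie. With a hypothetical group of T2DM patients with stroke and normal cognition (25 assumed), the four group terms have rank 4 of 4, and both effects can be estimated if they are additive.

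**Step 4: what the 30 VCI patients can offer.** All have had a stroke, so stroke status is constant among them. For a partial correlation with one covariate (lesion volume), the Fisher z standard error is 1/√(30 − 1 − 3) = 1/√26 = 0.196. For a true correlation near zero the 95% limits are about ±tanh(1.96 × 0.196) = ±0.37.

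**The case against.** The strongest reply is that vascular injury belongs to VCI by definition. The Introduction defines VCI through clinical stroke or subclinical vascular brain injury, and section 2.8.1 requires vascular findings on imaging. Comparing post-stroke VCI with stroke-free diabetes is then a legitimate descriptive contrast, with stroke status openly stated. That stands for a descriptive contrast. It does not make stroke inseparable from the diagnosis: the Introduction and section 2.8.2 both allow VCI without a clinical cerebrovascular event, and the stroke requirement enters only through the inclusion criterion in 2.9.1.

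It can also be said that the article never claims a VCI difference independent of stroke. This is largely right. Section 2.1 sets out only the treatment objective. The Discussion sentence linking volume change to cognitive impairment caused by T2DM summarises earlier studies, not results expected here. The fault is therefore a contrast whose permissible interpretation is left open, not a false conclusion already written down.

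A reader might go further and infer that lesions will not be masked in the image analysis. The documents do not support that. Section 2.29.2 names software and tests, and preprocessing is detail an article may leave to the full plan. Nor can one say flatly that hippocampal lesions are admitted. Section 2.12, item 3, excludes other focal injury affecting cognition, though its scope is unclear, since read literally it would also catch the qualifying strokes.

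**Conclusion.** The point holds for the two contrasts that involve the VCI group. Stroke and cognitive impairment are completely aliased there (30/30 against 0/50), and the listed covariates cannot separate them. This follows from the entry criteria alone and needs no outside assumption. How much of any observed hippocampal difference would be due to stroke cannot be determined from the documents: it could be some, all or none.

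A reader might want a false-positive rate. The documents give no hippocampal SD, lesion frequency or lesion size, so any such rate rests on assumptions. For example, assume an SD of 10% of the mean and 5 of 30 VCI patients each losing 20% of hippocampal volume. A single uncorrected two-sided 5% t test against 25 comparators is then positive in about 15% of simulated trials with no cognition-related difference. The article plans a three-group ANOVA with cluster-level correction, so that figure does not describe this trial and the conclusion does not rely on it.

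A reader might also infer that the treatment comparison is compromised. It is not biased by this.

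**What to change.** 1. In the Abstract (Methods/Design), section 2.2 and section 2.29.2, state that contrasts with the VCI group compare post-stroke cognitive impairment with T2DM against stroke-free groups with normal cognition. State that a difference will not be attributed to cognitive impairment in T2DM as distinct from stroke.
2. Address the hippocampus–cognition link within the 30 VCI patients, by relating baseline hippocampal measures to baseline MoCA and WMS-IV with adjustment for lesion volume measured on the baseline scans. Section 2.29.3 already plans correlations in these patients, but on regions found significant after treatment, which is a different question.
3. Add a sensitivity analysis of the three-group hippocampal contrast without VCI patients who have a visible hippocampal lesion. This checks for direct damage to the structure but does not remove the aliasing. The randomised comparison keeps all patients.

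The cost is rewording, lesion measurement on 30 scans already scheduled in Table 1, and a narrower claim from the first stage. The within-VCI analysis will be imprecise: 30 patients, and a range restricted by MoCA below 26, MMSE of at least 24 and CDR of 0.5. It should be labelled exploratory. No extra patients or scans are needed.

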### Inclusion criteria of healthy volunteers

2.11

1.Do not meet the diagnostic criteria for diabetes, and stroke is excluded as confirmed by CT or MRI.2.Cognitive function is normal, MoCA score ≥26 points (if the length of education is <12 years, 1 point is added to the test results to correct the cultural influence). MMSE score ≥24.CDR score is 0.IADL score ≥16.3.Can cooperate to complete fMRI scan.4.The range of age from 50 to 60 years’ old, right-handedness.5.Diseases without brain trauma, drug and alcohol dependence that may affect the structure and function of the brain, not accompanied by depression, mental symptoms and other diseases.

### Exclusion criteria

2.12

1.Subjects with obvious auditory, visual, and language impairments that affect cognitive function test.2.In the past 3 months, there are acute complications of diabetes such as diabetic ketoacidosis and deep coma, and serious diseases such as heart, lung, liver, kidney, and blood system may affect cognitive function.3.Subjects with central infection, brain tumor, or other focal injury affecting cognition suffer from Alzheimer disease, Parkinson disease, and other neurological diseases that can cause dementia. A history of severe traumatic brain injury with persistent neurological deficits or known structural abnormalities of the brain.4.The history of stroke is <3 months or >12 months.5.Suffered from depression in the past 2 years. the score of self-rating anxiety scale or self-rating depression scale > 50.6.Have a history of alcohol or drug abuse or dependence in the past 2 years.7.The following categories of drugs were used within 30 days before screening for cognitive impairment: drugs for the treatment of Alzheimer disease or dementia, anti-Parkinson disease drugs, short-acting antianxiety agents, nerve sedatives or analgesics, antiepileptic drugs, hormones, drugs with significant cholinergic or anticholinergic side effects.8.Those who were claustrophobic or failed to complete fMRI scans due to other reasons during the course of the test.

### Elimination criteria

2.13

These will include cases with violation of inclusion or exclusion criteria, patients included in the wrong treatment group, and patients who withdraw from the trials, use prohibited drugs or treatments in combination, and with insufficient data.

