### Sample size

2.5

We will conduct this study using a partial randomized controlled trial design, and the main observed outcome will be improvements in VCI patients with T2DM cognitive function. Our previous clinical observation found that 4 weeks of acupuncture-rehabilitation therapy treatment and routine drug therapy can improve scores on the MoCA scale by 3.13 ± 0.75 and 1.53 ± 0.33 points, respectively.^[5]^ Use PASS15.0 software to calculate, with the significance test level set at 0.05 and the test power at 0.9, the required sample size was 13 subjects for each group. Considering a dropout rate of 15%, a total of 30 subjects needed to be enrolled in VCI group with T2DM (15 participants per group). Then the Healthy volunteers group and T2DM group with normal cognitive function group were matched with the corresponding patient volume (25 participants per group). Therefore, a total of 80 subjects were included in this study.

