### Informed consent

2.15

Before the study, the general research process will be explained at the time of participant recruitment. Participants will be informed that participation in the trial is absolutely voluntary and that they can withdraw from the trial at any time. In the case of withdrawal, the collected participant study data will not be deleted and will be used for final analysis. Each participant should obtain and sign written informed consent before receiving any intervention related to this study.

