#### Statistical analysis of general data, behavioral tests, and blood biomarkers

2.29.1

The metrological data of the measured data were expressed as “mean ± standard deviation,” and the normality test was carried out. If all data were in line with normal distribution (*P* > .05), *χ*^2^ test was used for counting data, *t* test was used for measurement data, double-sample *t* test was used for comparison between the 2 groups, and paired-sample *t* test was used for comparison within the group. The test level was *P* = .05, if *P* < .05 indicated statistically significant difference. The above statistical work is analyzed and processed by specialized statisticians using SPSS25.0 statistical software (SPSS Inc, Chicago, IL).

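### The elimination list removes patients for post-randomisation events without confining this to a secondary analysis, and for withdrawers it conflicts with the consent section

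*Protocol article*

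**What the plan says.** Section 2.2 (Trial design) describes the randomised part: "30 VCI patients with T2DM were randomly divided into the experimental group and the control group". Section 2.5 (Sample size) puts 15 in each arm and allows for 15% dropout.

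Section 2.13 (Elimination criteria) opens with eligibility failures, "These will include cases with violation of inclusion or exclusion criteria", and continues with "patients included in the wrong treatment group, and patients who withdraw from the trials, use prohibited drugs or treatments in combination", and then insufficient data. It does not say what the patient is eliminated from.

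Section 2.15 (Informed consent) tells participants: "In the case of withdrawal, the collected participant study data will not be deleted and will be used for final analysis".

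Section 2.12 (Exclusion criteria), item 8, excludes "Those who were claustrophobic or failed to complete fMRI scans due to other reasons during the course of the test".

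Section 2.29.1 gives the tests for scales and biomarkers ("double-sample *t* test was used for comparison between the 2 groups, and paired-sample" t tests within groups). Sections 2.28 and 2.29 name no analysis set and do not refer back to section 2.13.

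**The concern.** A randomised comparison is protected only while patients are analysed in the arm to which they were allocated. Withdrawal, treatment in the wrong arm, prohibited co-treatment and incomplete data all become known after allocation, and each can depend on the treatment received and on how the patient is doing. Removing patients on those grounds compares completers and compliers.

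The design gives a reason to expect such dependence. The experimental arm has scalp needles retained for 6 to 8 hours, 6 days a week for 12 weeks, plus dual-task training. The control arm has drug treatment only. Participants know their arm (section 2.17). Section 2.25 stops all treatment after fainting, allergy or pain, and the article does not say whether such a patient then counts as withdrawn.

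With 15 per arm, each elimination removes about 7% of an arm (1/15 = 6.7%). Two incompatible instructions on withdrawers also leave open who is analysed until after the data are in.

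**Working it through.** **1. The sections side by side**

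| Ground in section 2.13 | Known when | Section 2.15 | Result |
|---|---|---|---|
| Eligibility violation | Concerns status before randomisation | Silent | Not the issue here |
| Withdrawal | After randomisation | Collected data kept and analysed | Direct conflict |
| Wrong treatment group | After randomisation | Silent | Departs from analysis as randomised |
| Prohibited drug or treatment | After randomisation | Silent | Departs from analysis as randomised |
| Insufficient data | After randomisation | Silent | Departs from analysis as randomised |

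**2. How many patients the plan expects to lose**

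Inputs from section 2.5: 13 required per group (26 in all), 15% dropout, 30 enrolled.
- The plan's own step: 26 × 1.15 = 29.9, rounded to 30. Dividing instead, 26 / 0.85 = 30.6, or 31. The stated 30 is reproduced by the first form.
- Expected loss per arm: 15 × 0.15 = 2.25, about 2. Elimination at that rate leaves about 13 v 13 (26) instead of 15 v 15 (30).

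**3. If elimination is unrelated to arm and outcome**

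Standard error of the difference, in SD units: √(2/15) = 0.365 with all randomised patients and √(2/13) = 0.392 after elimination. The ratio is 1.07, so intervals are about 7% wider and there is no bias.

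**4. If elimination is related to outcome in one arm**

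Assumptions not in the documents: normal outcome, no true effect, 15 per arm, two-sided t test at 0.05.
- The two lowest expected values in a standard normal sample of 15 are about −1.74 and −1.25. Removing both raises that arm's mean by (1.74 + 1.25)/13 = 0.23 SD.
- With no loss in the other arm, that is also the shift in the difference. Simulation of 40,000 trials gave 0.23 SD and a rejection rate of 10.9% in place of 5%.
- Milder case: about 14% lost in each arm, related to outcome in the experimental arm only. The shift is 0.13 SD and the rejection rate 6.0%.
- If both arms lose the same kind of patient at the same rate, the shifts cancel when there is no effect.

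**5. Exclusion item 8**

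Table 1 has fMRI at baseline and at week 12, and serum tests and scales at baseline and weeks 4, 8 and 12. Section 2.2 puts the first scan before randomisation. Item 8 does not say which scan it means. If it reached the week-12 scan, section 2.13 would eliminate that patient as an exclusion-criterion violation, together with serum and scale data already collected.

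**The case against.** Section 2.13 never says what a patient is eliminated from. Read as a per-protocol list, with section 2.15 governing the main analysis, both sections could be followed. Section 2.28 leaves a statistical analysis plan to a third party, and analysis sets usually belong there. This stands in part: the article does not prove that the main analysis will omit these patients. But the wrong-group and insufficient-data items make little sense except as removal from the data or the analysis. Silence on analysis sets would be no fault; here the article states a rule and leaves it unqualified.

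A reader might infer three stronger things that the documents do not support:
- **That section 2.15 promises an analysis of all randomised patients.** It speaks only of withdrawers.
- **That exclusion item 8 plainly covers the week-12 scan.** It stands in an eligibility list, is paired with claustrophobia and mirrors the inclusion item on being able to complete the scan. Its wording is ambiguous.
- **That the bias favours the experimental arm.** Needle burden could drive losses there, but unblinded controls could also leave or seek acupuncture elsewhere. The article gives one dropout rate and no split by arm.

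**Conclusion.** The point holds in limited form. Section 2.13 contains a rule that, if followed in the main analysis, removes randomised patients for post-randomisation events. On withdrawers it conflicts with section 2.15, and nothing in the article reconciles the two.

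The size depends on facts not in the documents. At the planned loss, the consequence ranges from intervals about 7% wider with no bias to a shift of about 0.23 SD. The upper figure assumes that exactly the 2 worst responders go from one arm and that the other has no comparable loss. The plan expects about 2 losses in each arm, so it is an illustration, not a forecast. A 3-of-15 case (20%) would exceed the planned 15%. The direction of any bias is unknown.

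**What to change.** - Reconcile sections 2.13 and 2.15 so that they give one rule for withdrawers' data.
- Define the main between-arm analysis as all randomised VCI patients in the arm assigned, using all data collected, including withdrawers' data up to withdrawal. For serum markers and scales, a repeated-measures model over baseline and weeks 4, 8 and 12 would do this without requiring a complete record. It assumes that missingness is explained by the data observed, and the plan should say so.
- Confine the section 2.13 list to a per-protocol sensitivity analysis.
- Clarify that exclusion item 8 refers to the scan before randomisation, so that a patient without a week-12 scan still contributes serum and scale data.

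The cost is rewording and a change of model for the serum and scale outcomes; no new data are needed. The estimate may be slightly less favourable. Week-12 VBM stays missing for patients without that scan, whichever analysis set is used.
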